# Comparing specialist medical care with specialist medical care plus the Lightning Process® for chronic fatigue syndrome or myalgic encephalomyelitis (CFS/ME): study protocol for a randomised controlled trial (SMILE Trial)

**DOI:** 10.1186/1745-6215-14-444

**Published:** 2013-12-26

**Keywords:** Fatigue, Paediatrics, Chronic fatigue syndrome, Myalgic encephalomyelitis

## Abstract

**Background:**

Chronic fatigue syndrome or myalgic encephalomyelitis (CFS/ME) is a relatively common and potentially serious condition with a limited evidence base for treatment. Specialist treatment for paediatric CFS/ME uses interventions recommended by National Institute for Health and Clinical Excellence (NICE) including cognitive behavioural therapy, graded exercise therapy and activity management. The Lightning Process® (LP) is a trademarked intervention derived from osteopathy, life-coaching and neuro-linguistic programming, delivered over three consecutive days as group sessions. Although over 250 children with CFS/ME attend LP courses each year, there are no reported studies on the effectiveness or cost-effectiveness.

**Methods:**

This pragmatic randomised controlled trial is set within a specialist paediatric CFS/ME service in the south west of England. Children and young people with CFS/ME (n = 80 to 112), aged 12 to 18 years old will be randomised to specialist medical care (SMC) or SMC plus the LP. The primary outcome will be physical function (SF-36 physical function short form) and fatigue (Chalder Fatigue Scale).

**Discussion:**

This study will tell us whether adding the LP to SMC is effective and cost-effective compared to SMC alone. This study will also provide detailed information on the implementation of the LP and SMC.

**Trial registration:**

Current Controlled Trials ISRCTN81456207 (31 July 2012).

## Background

The Royal College of Paediatrics and Child Health in the UK has defined chronic fatigue syndrome or myalgic encephalomyelitis (CFS/ME) as ‘generalised fatigue, causing disruption of daily life, persisting after routine tests and investigations have failed to identify an obvious underlying “cause”’ [1]. The NICE guidelines recommend a minimum time of three months of fatigue before making a diagnosis in children [2].

CFS/ME in children is a relatively common [3-6] and potentially serious condition with over 50% of children bedbound at some stage and a mean time off school of one academic year [7].

There is a limited evidence base for the treatment for children with CFS/ME. There is one randomised controlled trial (RCT) comparing cognitive behavioral therapy (CBT) (n = 29) and waiting list (delayed CBT) (n = 33) which reported improvements in fatigue, physical function and return to full time school in the early CBT arm [8,9]. However, in this study, approximately 40% of those in the early CBT arm did not have an improvement at five months. In an RCT comparing family-focussed CBT versus psycho-education [10] (n = 63) children in the CBT group were attending more school at discharge and three months post treatment but not at the primary outcome time point (6 months) [10]. Long-term follow-up (24 months) in this group showed that recovery (defined using fatigue and school attendance) was 79% in the family-focused CBT group compared with 64% in the psycho-education group [11]. A recent RCT comparing Internet based CBT (n = 68) with usual care (n = 67) showed more children in the CBT arm (75% versus 16%) attended full time school, did not have severe fatigue and had normal physical functioning (78% versus 20%) at six month follow-up [12].

The Phil Parker Lightning Process® (LP) is a trademarked intervention that is used for a variety of conditions including CFS/ME. It has been developed from osteopathy, life coaching and neuro-linguistic programming. The intervention includes three group sessions on consecutive days where young people are taught skills that they can try out for themselves including looking at their sitting and standing posture. Families currently pay approximately £620 to attend the LP course.

Even though over 250 children and young people a year use the LP as an intervention for their CFS/ME, there are currently no reported studies investigating the effectiveness or possible side effects (for example serious adverse events) of the LP.

This trial continues from the SMILE feasibility study which showed that recruitment, randomisation and data collection on health resource use was feasible and acceptable [13]. In this trial we will compare the effectiveness and cost-effectiveness of specialist medical care (SMC) plus the LP with SMC alone for children with CFS/ME.

### Hypothesis

We will test the null hypothesis that the addition of the LP to SMC has no additional benefit to SMC alone and is not cost-effective.

## Method

### Design

This is a pragmatic [14] randomised controlled trial comparing SMC plus the LP with SMC alone among children with CFS/ME. Qualitative research methods have been integrated into this study to ensure clear understanding of the processes (implementation, acceptability and setting of the interventions). See Figure 1 for trial flow diagram.

**Figure 1 F1:**
[figure not shown]
SMILE flow diagram.

### Population

Children and young people aged 12 to 18 years inclusive will be recruited after assessment by the Bath/Bristol paediatric CFS/ME service. This is a large regional and national service that currently provides assessment and treatment for over 250 children a year. The majority of referrals are from South Gloucestershire, Bristol, Somerset and West Wiltshire. Referrals are made by paediatricians, general practitioners and, in some cases, schools. Children are given a diagnosis of CFS/ME after a thorough assessment and screening blood tests according to guidelines produced by the National Institute for Health and Care Excellence (NICE) [2]. The majority of children referred into the service have CFS/ME as other causes of fatigue are usually excluded prior to referral. Approximately 10% of children referred into the service are housebound and are assessed at home.

### Inclusion/exclusion criteria

Children will be included if they have CFS/ME and are between 12 and 18 years old inclusive. Children will be excluded if: they are too severely affected to attend hospital appointments (defined as children and young people that do not regularly leave their house); or if they or their parents have insufficient English to either understand the patient information sheet and consent form to take part in the LP or the research interviews.

### Recruitment

Potentially eligible children and their families will be identified by the clinician conducting the initial clinical assessment who will inform them about the study and give both the young person and their parents patient information sheets. The clinician will obtain consent from the young person and their family to be contacted by a researcher. If willing, the recruiting researcher will contact the family and arrange to visit them at a convenient location (usually at home) to discuss and provide further information about the study.

### Randomisation

The recruiting researcher will explain the rationale for the study and its design, the uncertainties about the effectiveness of either intervention, the known advantages/disadvantages of the interventions, the options available outside the RCT, and the right not to take part in the study or to withdraw at any time. Willingness to participate will be ascertained, checking that both the young person and their family understand the study. Those willing to take part in the study will be asked to consent to randomisation and sign the consent form. The recruiting researcher will then telephone the automated randomisation service operated by the Bristol Randomised Trials Collaboration for the intervention allocation, which will be conveyed to the participant. Allocation will be minimised [15] by age and gender, and retain a random component to reduce risk of prediction of allocation. If for any reason the service is unobtainable, randomisation will be completed during the next working day and the participant will be told of the results by phone or in person.

### Interventions

•SMC: children and their families are offered a variety of treatment options that are recommended in NICE guidelines [2]. Typically this is centred around graded activity and involves a follow-up phone call at two weeks followed by family based rehabilitation consultations lasting one hour at approximately six weeks, three months, and four and a half months. The number and timing of the sessions are agreed with the child and family and varies depending on the needs and goals of the child. Children who have high levels of anxiety are offered three individual sessions of CBT every two weeks over a six week period. Other interventions such as graded exercise therapy (GET) [16] are available for children and young people if needed. The clinical team providing SMC are not informed by the research team to which trial arm a participant has been allocated.

•SMC plus the LP: in addition to the SMC detailed above, young people and their parents will be asked to read the information about the LP on the website [http://www.lightningprocess.com] or using information sheets. If the young person is well enough, they will be asked to read a book about the LP, given to them from the LP team, or listen to an audio book if preferable. Children/young people and their parents will be asked to complete an assessment form (which will take about ten minutes) where they are asked to identify their goals and describe what they learnt from reading the book. After this they will have a telephone call with a LP practitioner (usually approximately 20 minutes). This is used to check that the young person and their parents are happy about attending the course, checks the goals identified by the young person and is an opportunity for the young person and their parents to ask further questions. If the young person and their family are happy to continue, the young person will be given a date to attend a course.

•The course is three sessions on three consecutive days. Each session is three hours and forty-five minutes long. Group sessions will include three to five young people between 12 and 18 years of age who live within the region covered by the CFS/ME service. During the group, children and young people will receive a theory session and a practical session. The course is free to those participating in the trial.

1. The theory session will include taught elements on the stress response, how the mind-body interacts and how thought processes can be both helpful and negative. The language used by young people will be discussed and in some cases challenged. Young people will be encouraged to think about what they may be able to take responsibility for and change. The taught sessions are followed by a group discussion.

2. The practical session is used to put some of the skills learnt into practice. Young people identify a goal they wish to achieve (such as standing for longer) and are then given alternative ways to think about and prepare for this. This involves using different cognitive (thinking) strategies before and during the period in which achieving the goal is attempted. Young people are also asked to identify a goal wherein they can practise the strategies in the afternoon or evening. This goal will usually be short but could be an activity that is up to 30 minutes long.

3. The LP practitioner will then arrange two follow-up phone calls with the young person and parents within two weeks of the course and then approximately six to eight weeks later.

### ‘Outcome assessment’

The following self-completed inventories will be collected at the first clinical assessment (baseline), 3, 6 and 12 months: 11 item Chalder Fatigue Scale [17]; pain visual analogue scale; physical function short form (SF-36) [18]; the Spence Children’s Anxiety Scale (SCAS) [19]; the Hospital Anxiety and Depression Scale (HADS) [20] for children aged 14 and over, and the Euroqol (EQ-5D) [21] a five-item quality of life inventory. Children and young people are asked about school attendance and home tuition in a two-item inventory. We will ask for consent to check school attendance using school records at assessment, 3, 6 and 12 months. Follow-up questionnaires will be sent in the post with a stamped addressed envelope for self completion.

#### Primary outcome

The primary outcome will be the SF-36 physical function subscale analysed as a continuous variable collected at six months post-randomisation. The SF-36 will be scored as the sum of responses to the ten items, each of which is coded 0 for ‘Yes, limited a lot’, 5 for ‘Yes, limited a little’ and 10 for ‘No, not limited at all’. This yields a score varying from 0 (for the highest level of disability) to 100 for no disability. The SF-36 physical function subscale will be used as we are primarily interested in change in physical function. It has been used in studies of adolescent CFS/ME [22] and in CFS trials in adults [16]. We chose six months as this was the first time that all those randomised to LP and SMC will have received LP. Secondary outcome measures will be school attendance, calculated as a percentage of expected sessions, at 3, 6 and 12 months; the SF-36 (physical function) at 3 and 12 months; the Chalder Fatigue Scale score at 3, 6 and 12 months; pain visual analogue scale at 6 months and quality adjusted life years (QALYs, derived from the EQ-5D) over the 12 month follow- up period.

### Measures used for economic evaluation

Parent(s)/guardian(s) will be asked to complete three inventories at the start of the trial (just after randomisation) and at 3, 6 and 12 months. These include an adapted four-item Work Productivity and Activity Impairment Questionnaire: General Health V2.0 (WPAI:GH) [23] and a resource use questionnaire assessing health service (for example, GP or specialist care), educational service (for example, school counsellor) use and travel costs most relevant to the CFS/ME population (all included in Additional file 1 and Additional file 2).

#### Non-responders

Those who have not replied within one week of each mail out will be sent a reminder letter requesting that the original set of questionnaires is completed and returned. A reduced set of questionnaires (comprising SF-36, Chalder Fatigue Scale score and school attendance inventory) with a stamped addressed envelope will also be included in case the originals have been mislaid. After another two weeks, those not returning any questionnaires will be telephoned by a researcher who will invite the respondent to complete the reduced questionnaire set over the telephone.

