### Economic evaluation

The economic evaluation will gather information on the costs to the NHS, other government agencies and wider society of the interventions in the two arms of the RCT. The primary cost-effectiveness analysis will compare incremental differences in NHS (including LP referral costs) and other public sector costs with any health gains achieved over 12 months, measured in QALYs. We will estimate the net monetary benefit of specialist medical care plus the LP compared to specialist medical care alone and quantify uncertainty using confidence intervals, cost-effectiveness acceptability curves and sensitivity analyses [27]. In secondary analyses we will tabulate the wider costs, including travel and productivity costs and consequences, including school time missed, in a cost consequence study [28,29].

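### The fallback questionnaire set for non-responders omits the EQ-5D and lists no parental cost form, so the economic data set can be smaller and more selected than the clinical one

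*Protocol article*

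**What the plan says.** Under Non-responders, families who have not replied within a week of a mail-out "will be sent a reminder letter requesting that the original set of questionnaires is completed and returned". The same letter encloses a fallback: "A reduced set of questionnaires (comprising SF-36, Chalder Fatigue Scale score and school attendance inventory". Two weeks later a researcher telephones those who have returned nothing and "will invite the respondent to complete the reduced questionnaire set over the telephone".

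Under Outcome assessment, the child's EQ-5D belongs to the full set: "The following self-completed inventories will be collected at the first clinical assessment (baseline), 3, 6 and 12 months". The Primary outcome section lists among the secondary outcomes "quality adjusted life years (QALYs, derived from the EQ-5D) over the 12 month follow- up period". Under Economic evaluation, the primary cost-effectiveness analysis sets NHS and other public sector costs "with any health gains achieved over 12 months, measured in QALYs". The Hypothesis section makes cost-effectiveness part of what the trial tests.

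The parents' forms (resource use, and work productivity and activity impairment) are described under Measures used for economic evaluation. Parents are "asked to complete three inventories at the start of the trial (just after randomisation", and again at 3, 6 and 12 months. Under Randomisation, the researcher telephones the service "for the intervention allocation, which will be conveyed to the participant".

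**The concern.** The fallback set is built around the clinical outcomes. It secures the primary outcome, fatigue and school attendance, but not the instrument from which every QALY is derived. A family that has been reached, and may be on the telephone, is not asked five questions that the primary economic analysis needs. No later analysis can recover an answer that was never requested.

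The people affected are those who needed chasing, and they may differ from the rest in health or in engagement with treatment. The economic comparison could therefore rest on fewer and more selected participants than the clinical comparison. The cost side may have the same gap, because the parents' resource-use form is not listed in the fallback either.

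A smaller matter is the timing of the parents' first forms. If they are completed once the allocation is known, their content or completeness could differ by arm, and they would be less useful as start-of-trial values.

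**Working it through.** **Inputs from the article**
- Fallback set: SF-36, Chalder Fatigue Scale, school attendance (Non-responders).
- EQ-5D at baseline, 3, 6 and 12 months (Outcome assessment); QALYs derived from it over 12 months (Primary outcome).
- 32 to 50 analysable per arm, 10 to 20% non-collection of the six-month primary outcome, 80 to 112 recruited (Sample size).

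**Inputs assumed**
- r, the share of participants answering only by the fallback set at each follow-up: 5%, 10%, 15%. The article gives no figure.
- A complete QALY needs the EQ-5D at all three follow-ups, and the baseline EQ-5D is complete.
- For the headcounts, the non-collection rate d applies at every wave. The article states it for six months only.

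**Step 1: the plan's own figure.** Recruited = analysable / (1 − d). 64 / (1 − 0.20) = 80, and 100 / (1 − 0.10) = 111.1, rounded up to 112. The target reproduces and is not in dispute. Its allowance concerns the SF-36 and does not bound missing EQ-5D data.

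**Step 2: what each route delivers**

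| Route at a follow-up | SF-36, fatigue, attendance | EQ-5D |
|---|---|---|
| Full set, returned at once or after the reminder | yes | yes |
| Fallback set by post only | yes | no |
| Telephone | yes | no |
| Not reached | no | no |

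The second and third rows are the gap.

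**Step 3: share without a complete QALY because of the fallback set alone**
- Same people each time: r, that is 5%, 10%, 15%.
- Independent between waves: 1 − (1 − r)³, that is 1 − 0.95³ = 14.3%; 1 − 0.90³ = 27.1%; 1 − 0.85³ = 38.6%.

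**Step 4: headcounts.** SF-36 at six months = N(1 − d). EQ-5D at one wave = N(1 − d − r). EQ-5D at all three waves = N(1 − d − r) if the same people are missing each time, and N(1 − d − r)³ if independent.

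| N, d | r | SF-36 at 6 months | EQ-5D at one wave (also all three, same people) | EQ-5D at all three, independent |
|---|---|---|---|---|
| 112, 10% | 0 | 101 | 101 | 82 |
| 112, 10% | 5% | 101 | 95 | 69 |
| 112, 10% | 10% | 101 | 90 | 57 |
| 112, 10% | 15% | 101 | 84 | 47 |
| 80, 20% | 0 | 64 | 64 | 41 |
| 80, 20% | 5% | 64 | 60 | 34 |
| 80, 20% | 10% | 64 | 56 | 27 |
| 80, 20% | 15% | 64 | 52 | 22 |

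Only the fall from the r = 0 row is due to the fallback set; the rest is ordinary non-response.

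**Step 5: timing of the parents' first forms.** No arithmetic applies. The Randomisation section has the allocation obtained by telephone and then passed on. The economic measures section places the parents' first forms just after randomisation. Read together, parents probably know the allocation when they answer. This is a close inference, since the article does not say where or how the forms are completed. The child's baseline EQ-5D is taken at the first clinical assessment, before randomisation, so it is unaffected.

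**The case against.** The fallback is a deliberate trade-off. It protects the primary outcome and two secondary outcomes among people who have so far returned nothing, and a short form is more likely to be answered. It discards no EQ-5D already in hand. QALYs are listed as a secondary outcome, and this is neither a contradiction nor an error. All of that stands, but five items add little length and they feed the primary economic analysis.

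A reader might infer that only prompt responders will have QALYs. The article does not support that: the reminder asks again for the full set, and anyone who then returns it supplies the EQ-5D.

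A reader might also take 14 to 39% as the expected loss, or add it to the 10 to 20% allowance. Neither follows. Those percentages assume both the rate and independence between waves. Late responders are likely to be partly the same people, which moves the loss towards 5 to 15%. The 10 to 20% is a single-wave allowance for a different instrument.

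Imputation is planned as a sensitivity analysis under Data analysis, and the same-wave SF-36 and fatigue scores could inform it. This is a real mitigation. The article does not state it specifically for the economic analysis, however, and an imputed utility is a weaker substitute for an obtainable answer.

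On the parents' forms, a reader might infer that the primary cost-effectiveness result is biased. The documents do not support that. No adjustment of costs for start-of-trial values is stated, productivity and travel costs enter only secondary tabulations, and the baseline EQ-5D precedes randomisation.

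**Conclusion.** The point holds as a cheap improvement to data collection. For anyone reached only through the fallback set or the telephone call, the EQ-5D is missing at that wave although the clinical outcomes are obtained. The direction is certain. The size is not, because the article gives no rate of fallback-only response.

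Under assumed rates of 5%, 10% and 15% per wave, the share lacking a complete QALY is 5%, 10% and 15% with full overlap between waves and 14%, 27% and 39% with independence. With 112 recruited, 10% non-collection and a 10% fallback-only rate, about 101 participants give the six-month SF-36 and about 90 the EQ-5D. Any difference between arms cannot be derived from the document. The cost data may have a similar gap, since the parents' resource-use form is not listed in the fallback.

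The timing of the parents' first forms is a minor companion point whose effect cannot be sized. Neither point shows that the cost-effectiveness comparison is invalid.

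**What to change.** Add the five-item EQ-5D and a short resource-use form for parents to the reduced postal set and to the telephone script. Adding the EQ-5D alone would leave late responders potentially without costs. The price is a slightly longer form or call for people already slow to reply. Asking the SF-36, fatigue and attendance items first would protect the clinical outcomes if a call is cut short.

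As a minor companion change, have parents complete their first economic forms after consent and before the randomisation call. They can then serve as start-of-trial values free of knowledge of the allocation. If the forms can be completed at the recruitment visit, this is only a change of order and nearly free; the article does not say where they are completed, so that should be confirmed.
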